### Timing of the final analysis

The final analysis is scheduled for when 55 primary events have occurred, which is anticipated once the last patient recruited has undergone 2 years of follow-up (please see section on “sample size”). The Steering Committee will decide whether to shorten follow-up if 55 primary events have occurred before 2 years of follow-up for all patients or before 1500 patients have been enrolled. Contrarily, the Steering Committee may opt to extend follow-up if fewer than 55 events have occurred once the last enrolled patient has 2 years of follow-up.

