### Analysis methods

The respective investigators gather data from each site, and primary and secondary analyses will be performed centrally.

The primary analyses rely on time-to-event (survival) statistics.

The possible events are as follows:I.Primary outcome occurrenceII.DeathIII.Withdrawal of consentIV.Last contact (loss to follow-up)V.Trial end*

*The time frame is at least 2 years from index surgery; thus, follow-up continues for all patients until the last enrolled patient has been followed for 2 years.

The time between randomization and event (I–V) is the exposure time.

The primary analyses will be based on the ITT principle, i.e., it includes all randomized patients with an available baseline assessment independently of the performed surgery.

PP analyses will serve as sensitivity analyses.

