#### Analyses of the primary outcome

Cumulative incidence (Aalen-Johansen) plots will display results of the primary outcome with death as a competing risk. Gray’s test for differences between cumulative incidence rates will be used to assess statistical significance.

As the primary outcome will be examined in a competing risk setting, cause-specific Cox regression is used to quantify the difference in risk between allocation groups. The main covariate is randomization (LAA closure vs. open LAA). The analysis will be adjusted for the stratification factors before randomization, i.e., site, surgery type, and OAC therapy. The results will be presented as hazard ratio (HR) with 95% confidence intervals.

The null hypothesis is that there is no difference between the cumulative incidence rates of the two treatment groups.

The decision rule for the hazard ratio is as follows:

VI.Superiority of LAA closure will be accepted if the estimated HR is < 1 and the 95% confidence interval (CI) does not include 1VII.Superiority of open LAA will be accepted if the estimated HR is > 1 and the 95% CI does not include 1VIII.No superiority will be accepted if the 95% CI contains 1

Proportional hazard assumptions for the Cox regression models will be tested by interaction terms with time on study, weighted Schoenfeld, and cumulative Martingale residuals. If non-proportionality is detected for covariables used for adjustment (site, surgery type, and OAC therapy), these factors will be included as stratification variables. If non-proportionality is detected for the primary exposure (randomization), time-varying hazard ratios with 95% confidence intervals will be used to assess the differential effect of randomization as a function of time-on study.

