**Table Tabe:** 

Item	Time frame
Bleeding (BARC 3a, 3b, 4)^*^	Within 30 days from index surgery
Infection	
Redo cardiac surgery^#^	
Re-hospitalization due to • Pericardial effusion • Pleural effusion • Pericardial infection • Acute decompensated heart failure • Bleeding (BARC 2–4)^*^	30 days from index surgery until the end of follow-up

^*^The Bleeding Academic Research Consortium (BARC) criteria define bleeding events [21]. ^#^Including redo surgery due to device failure or injury caused by device placement

All randomized patients undergoing index surgery will be included in the safety analysis data set. The number and frequencies of the adverse events in each allocation group will be presented in tables alongside descriptive statistics.

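### Re-hospitalization harms are counted over unequal lengths of follow-up but reported only as numbers and frequencies, so their absolute size refers to no fixed period

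*SAP article*

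**What the plan says.** The safety table in the Harms section has two kinds of window. One is fixed: "Within 30 days from index surgery". The other applies to the re-hospitalization block (pericardial effusion, pleural effusion, pericardial infection, acute decompensated heart failure, BARC 2–4 bleeding) and is open-ended: "30 days from index surgery until the end of follow-up". On the analysis set the section says "All randomized patients undergoing index surgery will be included in the safety analysis data set", and on the summary "The number and frequencies of the adverse events in each allocation group will be presented in tables alongside descriptive statistics". It names no person-time measure, time horizon or handling of censoring and death.

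Four other places determine how long a patient is at risk:

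- Analysis methods: "follow-up continues for all patients until the last enrolled patient has been followed for 2 years". Two years is thus the minimum.
- Timing of the final analysis, on shortening: "The Steering Committee will decide whether to shorten follow-up if 55 primary events have occurred before 2 years of follow-up for all patients". On lengthening: "the Steering Committee may opt to extend follow-up if fewer than 55 events have occurred".
- Adherence and protocol deviations: a patient whose LAA is closed later on clinical indication stops follow-up at that moment.
- Withdrawal/follow-up, and the event list in Analysis methods: data collection ends at withdrawal of consent, and death and last contact end exposure.

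For stroke the plan does handle unequal follow-up: "Cumulative incidence (Aalen-Johansen) plots will display results of the primary outcome with death as a competing risk".

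**The concern.** A proportion with an event is a risk only if everyone could be observed over the same period. In the re-hospitalization block, one patient may have 2 years of opportunity for an event, another 2 years plus the whole accrual period, and a third only a few weeks before death. The tabulated frequency then averages over these lengths. It grows with the time accrual takes, and it moves with Steering Committee decisions that depend on the stroke count.

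Safety is one of the secondary objectives, and the Framework section gives it a hypothesis of no difference. The trial asks whether closure is worth adding in patients who may have a low stroke risk. A reader will want to weigh an absolute harm against an absolute stroke benefit over the same period. The planned stroke curve allows a value to be read at 2 years; nothing planned for these harms does.

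**Working it through.** **The plan's own figures.** The SAP gives no figure for the harms. For stroke it works in 2-year risks. The Sample size section has 1.2% and 3.0% per year for 2 years, so 2 × 1.2% = 2.4% and 2 × 3.0% = 6.0%. With 1302 / 2 = 651 per arm, expected events are 651 × 0.024 = 15.6 and 651 × 0.060 = 39.1, matching the stated 16 and 39 (total 55). The planned benefit is thus 6.0 − 2.4 = 3.6 percentage points at 2 years, and a harm has to be on that scale to be compared with it.

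**Inputs for the harms (all assumed).** The SAP gives neither the accrual time nor any readmission or death rate. Let accrual be uniform over A years, so that follow-up is uniform on 2 to 2 + A years. Let readmission have hazard λ and death hazard μ = 0.03 per year.

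**Case 1: constant hazard.** The cumulative incidence of a first readmission by time t is

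F(t) = λ/(λ+μ) × [1 − exp(−(λ+μ)t)].

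The expected crude frequency is its average over follow-up times:

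C(A) = λ/(λ+μ) × {1 − [exp(−2k) − exp(−(2+A)k)]/(kA)}, with k = λ+μ.

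For λ = 0.04, k = 0.07:

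- F(2) = 0.5714 × (1 − 0.8694) = 0.075.
- A = 3: C = 0.5714 × [1 − (0.8694 − 0.7047)/0.21] = 0.123.
- A = 6: C = 0.5714 × [1 − (0.8694 − 0.5712)/0.42] = 0.166.

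| λ per year | 2-year risk | Crude, A = 3 | Crude, A = 5 | Crude, A = 6 | Ratio to 2-year risk, A = 3 to 6 |
|---|---|---|---|---|---|
| 4% | 7.5% | 12.3% | 15.2% | 16.6% | 1.65 to 2.2 |
| 2% | 3.8% | 6.4% | 8.0% | 8.7% | 1.7 to 2.3 |

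With shorter accrual the ratio at λ = 4% is 1.23 (A = 1) and 1.44 (A = 2). A variant that starts the clock at day 30, ignores death and takes λ from 2% to 10% gives 1.4 to 2.5 over A = 2 to 6. The upper end therefore shifts somewhat with the assumed rates.

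**Case 2: readmissions cluster early.** Suppose the hazard halves every 6 months. Two years is 4 half-lives, so 1 − 2⁻⁴ = 0.9375 of all the hazard a patient will ever accumulate falls within 2 years. For a rare event, the crude frequency can then exceed the 2-year risk by at most 1/0.9375 = 1.07, however long accrual takes. With faster decay the ratio approaches 1.0.

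**Comparison of arms.** Take a constant hazard from day 30 of 7.5% against 5% per year (assumed hazard ratio 1.5) and death at 3% per year in both arms.

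| | At 2 years | Crude, A = 3 | Crude, A = 5 |
|---|---|---|---|
| Risk ratio | 1.47 | 1.44 | 1.42 |
| Risk difference (points) | 4.1 | 6.5 | 7.7 |

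The ratio hardly moves. The absolute difference grows by a factor of 6.5/4.1 = 1.6 to 7.7/4.1 = 1.9.

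**The case against.** Five points can fairly be made against the concern.

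1. *Counts and frequencies by arm are the usual safety summary, the outcomes are unpowered, and a journal article need not give table layouts.* This limits the severity. But the article does state the summary for this block and states the open window beside it. A general promise of descriptive statistics names no rate or horizon.

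2. *Randomization balances follow-up.* This stands. Allocation is 1:1 in blocks within strata that include site, so enrolment dates should be similar in both arms. A reader might infer that the comparison of arms is biased. The documents do not support that, and the example moves the ratio only from 1.47 to 1.42–1.44. What remains is any difference between arms in death or in halting for later closure. Halting would be expected mainly in the open-LAA arm, but the SAP gives no size for it.

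3. *Efficacy also runs beyond 2 years.* This stands too. A reader might infer that benefit is strictly a 2-year quantity while only harm is counted for longer. The outcome tables do give 2 years, but Analysis methods makes that a minimum, and the hazard ratio uses the longer follow-up. The narrower contrast is that a 2-year stroke risk can be read from the planned curve, and no such curve is planned for these harms.

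4. *Stroke does not shorten safety follow-up.* A reader might infer that it does, since the primary outcome ends exposure in Analysis methods. That rule concerns the time-to-event analyses of efficacy. Nothing in the Harms section or in the timing of safety assessments says that safety recording stops at a stroke.

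5. *The inflation may be negligible.* Pericardial effusion, pleural effusion and pericardial infection could well occur mostly early. This stands as an equally admissible assumption, so the lower end of the range is about 1.0.

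**Conclusion.** The point holds for the re-hospitalization block only, as a cheap improvement. Its absolute frequencies and differences refer to no fixed period, because length of follow-up varies with enrolment date, Steering Committee decisions and individual stops. The rows with a 30-day window are unaffected.

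It would go too far to say that each patient has a different end date. Apart from individual stops, follow-up closes for all at one calendar point, and what differs is the time since surgery. It would also go too far to say that the harm comparison as a whole is invalid, since the ratio between arms is nearly preserved.

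The size cannot be fixed from the SAP. The crude frequency could be about 1.0 times the 2-year risk with early clustering, or up to about 2.2 times with a constant 4% per year hazard, death at 3% per year and 6 years of accrual. Other assumed constant rates push the top slightly higher. These cases all assume at least 2 years of potential follow-up; a decision to shorten follow-up would lower the crude frequency.

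**What to change.** In the Harms section, for the rows whose window runs to the end of follow-up, add by allocation group:

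- the Aalen-Johansen cumulative incidence at 2 years of the first event after day 30, with death as competing event and a 95% confidence interval;
- the number of events per 100 patient-years, with person-time ending at death, withdrawal, last contact, later LAA closure or trial end.

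Keep the counts beside these. Leave the 30-day rows as number and percentage.

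The estimator is already specified for the primary outcome, so the change needs a few sentences of SAP text and little extra code. The costs are a longer safety table and the need for a date for each readmission; the article does not say whether these dates are recorded, so this should be confirmed.

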### Statistical software

The most recent version of RStudio (Boston, MA, USA) will be used for statistical analysis.

## Abbreviations

AF: Atrial fibrillation or flutter
BARC: Bleeding Academic Research Consortium
CABG: Coronary artery bypass grafting
CI: Confidence interval
CONSORT: Consolidated Standards of Reporting Trials
CT: Computed tomography
ECG: Electrocardiogram
HR: Hazard ratio
ITT: Intention-to-treat
LAA: Left atrial appendage
LAACS: Left atrial appendage closure by surgery
MRI: Magnetic resonance imaging
OAC: Oral anticoagulation
PP: Per-protocol
SCI: Silent cerebral infarction
TIA: Transient ischemic attack
